### Intervention measures

2.6

Both groups will receive the same drug regimen and different care regimens during treatment.

Observation group: receive cluster nursing, including: ① expectoration nursing: Introduce the importance of expectoration to patients, improve their compliance, and correctly guide the cough method. If effective cough expectoration cannot be achieved, expectoration can be carried out by slapping the back, beating and aerosol inhalation.^[16]^② Walking training: Nursing staff instructs patients to walk a short distance indoors, and the time and distance of walking can be extended after patients are gradually adapted to it. During the training, patients will stop training immediately if they have dyspnea or chest pain.^[17]^③ Posture nursing: In order to ensure normal and smooth breathing of patients, patients’ posture should be dynamically adjusted in combination with their physical status, mainly sitting and semi-reclining.^[18]^④ Psychological nursing: provide psychological counseling and care to patients, eliminate their negative emotions, and encourage them to maintain their optimistic attitude.^[19]^⑤ Dietary guidance: Patients will be given dietary guidance to reduce the intake of stimulating food, eat less and eat more frequently, and maintain a healthy and reasonable diet.^[20]^

The control group will receive routine nursing mode, including daily nursing and health guidance.

### Evaluation criteria and efficacy judgment

2.7

(1)Main outcome indicators: ① Total rate of improvement in cardiac function (refer to the principle of clinical research on treating heart failure with new Chinese Medicine)^[21]^; Excellent: heart failure is essentially ameliorated or the NYHA classification increased by at least 2 levels; Valid: NYHA classification increased by 1 level; Invalid: NYHA classification remain the same before and after the treatment; Worsened: NYHA classification decrease by at least. ② Minnesota Living with Heart Failure Questionnaire,^[13]^ the higher the score, the worse the patient's quality of life.(2)Secondary outcome indicators: left ventricular ejection fraction, N-terminal pro-brain natriuretic peptide, tumor necrosis factor-α, IL- 6, 6-minute walk test.(3)Adverse reactions: including abnormal liver and kidney function and any uncomfortable symptoms (such as dizziness, nausea, etc) during treatment.

The above observation indicators will be collected on the day before and after treatment. All patients will be followed up for 3 months, and data will be collected according to the same criteria in the first and third months.

### Data collection and management

2.8

The data involved in this study will be collected by 2 research assistants, and summarize and analyze by a statistician and a data analyst. Personal information about potential and registered participants will be collected, shared, and kept in a separate storage room to protect confidentiality before and after the trial.

### Statistical analysis

2.9

SPSS 25.0 (Chicago, IL) software will be used for statistical analysis of the collected data. Chi-square test will be used for counting data; measurement data is represented by $\bar{\text{x}}\pm \text{S}$, the independent sample *t* test is used for normal distribution, non-parametric test is used for skewness distribution. When *P* < .05, the difference is statistically significant.

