### Sample size

2.3

The calculation of sample size is based on mean and standard deviation of scores of Minnesota Living with Heart Failure Questionnaire^[13]^ after treatment. According to the results of the pilot study, the observation group will be 27.91 ± 4.31, and the control group will be 31.12 ± 4.85. Set α = 0.025, unilateral test, β = 0.20. According to the calculation of PASS15.0 software, 34 participants are needed in each group, the estimated withdrawal rate is 10%, so that 38 participants will be included in each group.

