### Study design

2.5

Subjects meeting inclusion and exclusion criteria will be randomly assigned to control and observation groups in a 1:1 ratio using a central network randomization tool. Random sequences will be generated using SAS 9.3 software (SAS Institute, Cary, NC) by independent statisticians not involved in the treatment process and statistical analysis of the data. Randomization will be performed without any stratification. The clinical study coordinator enters the subject information on a tablet computer and is given a random number. The research assistant gets the subject assignment information from the computer. Throughout the trial, the research assistant is responsible for recruiting, screening, and assigning random numbers to those who have been enrolled in the study. None of the research assistants, intervention supervisors, or those performing statistical analysis are aware of the group assignment.

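### The MLHFQ comparison leaves out the baseline score that the trial collects: a valid test that meets its power target, but less precise than it could be at no extra cost

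*Protocol article*

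**What the plan says.** Section 2.9 (Statistical analysis) fixes one rule for all measurement data: "the independent sample *t* test is used for normal distribution, non-parametric test is used for skewness distribution". It names no covariate, no change score, no criterion for judging normality and no particular non-parametric test.

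Section 2.3 (Sample size) shows which MLHFQ value is meant. The calculation rests on the "mean and standard deviation of scores of Minnesota Living with Heart Failure Questionnaire^[13]^ after treatment", with the expectation that "the observation group will be 27.91 ± 4.31, and the control group will be 31.12 ± 4.85", and then: "Set α = 0.025, unilateral test, β = 0.20". It concludes that "34 participants are needed in each group" and that "the estimated withdrawal rate is 10%, so that 38 participants will be included in each group".

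Section 2.7 lists MLHFQ as one of two main outcomes and sets the timing: "The above observation indicators will be collected on the day before and after treatment", with further collection at months 1 and 3. A baseline MLHFQ score is therefore planned for every patient. Section 2.5 adds: "Randomization will be performed without any stratification".

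**The concern.** Taken together, sections 2.3 and 2.9 give an unadjusted two-group comparison of MLHFQ after treatment. A questionnaire score before treatment usually predicts the same score a few weeks later. Variation between patients that the baseline could explain is then left in the error term, and the treatment difference is estimated with a wider interval than the collected data allow. Allocation is unstratified with 38 per group, so the design does nothing to balance baseline severity beyond randomisation.

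A second, smaller matter sits in the same sentence of section 2.9. Because the observed distribution decides between a t test and a rank test, neither the test nor the quantity estimated (a mean difference or a rank comparison) is settled before the data are seen.

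At stake is precision on a main outcome in a small trial. The validity of the result is not in question.

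**Working it through.** **Inputs.** Means 27.91 and 31.12, SDs 4.31 and 4.85, one-sided α 0.025, power 80%, 34 evaluable per group, 10% withdrawal (all section 2.3). The correlation r between baseline and post-treatment MLHFQ is not in the document; 0.3, 0.5 and 0.7 are assumed, with 0 as the limiting case.

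**Step 1: reproduce the plan's figure.**
- Difference: 31.12 − 27.91 = 3.21.
- Pooled SD: √[(4.31² + 4.85²)/2] = √21.05 = 4.588. Standardised difference: 3.21/4.588 = 0.70.
- Unadjusted two-sample t test, noncentral t distribution: 34 per group is the smallest size that reaches 80%, with power 81.1%. The normal approximation gives 33.
- Withdrawal: 34/0.9 = 37.8, rounded up to 38.

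The plan's 34 and 38 are reproduced exactly by an unadjusted t test on post-treatment scores. This supports that reading of the MLHFQ analysis.

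**Step 2: add baseline MLHFQ as a covariate.** The residual SD becomes 4.588 × √(1 − r²), and one further degree of freedom is used (65 instead of 66).
- Standard error of the difference: residual SD × √(2/34). Unadjusted: 4.588 × 0.2425 = 1.113.
- Noncentrality: 3.21 / standard error.
- 95% half-width: t quantile (1.997 for 65 or 66 df) × standard error.
- Equivalent gain in patients: 1/(1 − r²) − 1.

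| Analysis | Standard error | Noncentrality | Power at 34 per group | 95% half-width | Equivalent extra patients |
|---|---|---|---|---|---|
| Unadjusted t test | 1.113 | 2.88 | 81.1% | 2.22 | – |
| ANCOVA, r = 0 | 1.113 | 2.88 | 81.1% | 2.22 | 0% |
| ANCOVA, r = 0.3 | 1.061 | 3.02 | 84.6% | 2.12 | 10% |
| ANCOVA, r = 0.5 | 0.964 | 3.33 | 90.7% | 1.92 | 33% |
| ANCOVA, r = 0.7 | 0.795 | 4.04 | 97.8% | 1.59 | 96% |

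**Step 3: would change scores do as well?** With equal SDs before and after treatment, the variance of a change score is 2(1 − r) times that of the raw score. Power at 34 per group is then 67.1%, 81.1% and 95.6% for r = 0.3, 0.5 and 0.7. Each is below ANCOVA, and the first is below the unadjusted test.

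**Step 4: does choosing the test from the data do harm?** This was simulated with 34 per group and 20,000 runs, using the t test if both groups passed Shapiro-Wilk and Mann-Whitney otherwise, at two-sided 5%. Type I error was 4.96% with normal data and 5.0% with lognormal data. Power with normal data was 80.7%, against 80.9% for the t test alone.

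**The case against.** The strongest reply is that nothing is wrong with the stated test. Under randomisation an independent-sample t test is unbiased and holds its error rate, and section 2.3 sizes the trial for that same comparison with power above the target. All of this stands. A reader might infer that unstratified allocation lets baseline imbalance bias the result. It does not: chance imbalance is random error that the t test's standard error already covers. Adjustment makes that error smaller.

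A reader might also infer that choosing between a t test and a rank test after seeing the data loses power or inflates type I error. The simulation above shows next to no effect on either. What remains is that the test and the estimand are not fixed in advance. The missing normality criterion and the unnamed rank test are details that a condensed article may leave to another document.

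Thirdly, section 2.9 does not say which value enters the test. For MLHFQ, section 2.3 settles it. For ejection fraction, NT-proBNP, TNF-α, IL-6 and 6-minute walk, no section does; that they are compared as raw post-treatment values is an inference. The second main outcome, improvement in NYHA class, is defined relative to the pre-treatment class, so this point does not reach it.

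Finally, the gain depends on a correlation that the article does not report. This too stands, which is why a range is shown. At r = 0.3 the gain is only 3.5 percentage points of power.

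The reply that this is merely detail left to an analysis plan does not stand for MLHFQ. The article names a specific test, and that test uses no baseline.

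**Conclusion.** The point holds as one of efficiency. The MLHFQ analysis is valid and meets its own 80% target, with 81.1% power at 34 per group. It leaves unused a baseline score that is already being collected. Using it would raise power by about 3 to 17 percentage points and narrow the 95% half-width from 2.22 to between 2.12 and 1.59 points, for an assumed correlation of 0.3 to 0.7. If the correlation were zero, the cost would be negligible.

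These figures rest on the plan's pilot means and SDs, 34 evaluable patients per group, and a linear relation with a common slope in both groups. Bias, inflated error, a shortfall in power, and lost power from the choice of test are not supported and should not be claimed.

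**What to change.** - **MLHFQ.** Make ANCOVA with treatment and baseline MLHFQ the pre-specified analysis at the end of treatment. A mixed model over the post-baseline visits, with baseline MLHFQ as covariate and the contrast at the end of treatment, is an acceptable alternative. Report the adjusted mean difference with its 95% confidence interval whatever the observed distribution looks like.
- **Rank test.** Name it and keep it as a sensitivity analysis, so that the main estimand no longer depends on the data.
- **Secondary measurements.** Apply the same model to ejection fraction and 6-minute walk, and on the log scale to NT-proBNP, TNF-α and IL-6, reported as geometric mean ratios. If the sponsor intends something other than raw post-treatment values for these, the text should say so.
- **Sample size.** No change is needed. The 34 evaluable per group can stand as conservative. If the pilot recorded baseline scores, the correlation can be taken from it to replace the assumed range.

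The cost is a change of wording in section 2.9 and in any analysis plan, made before the data are seen. SPSS 25.0, the software already named, fits these models. No new data or patients are required.

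### Two unranked main outcomes, each judged at P < .05, in a trial sized for one test: if either alone counts as a positive result, the false-positive risk at end of treatment is about 8–10%, not 5%

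*Protocol article*

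**What the plan says.** Three sections of the protocol article bear on this.

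- **Section 2.7, Evaluation criteria and efficacy judgment.** There are two main outcomes in one numbered list, with no order of importance: "Main outcome indicators: ① Total rate of improvement in cardiac function" and "② Minnesota Living with Heart Failure Questionnaire,^[13]^ the higher the score, the worse the patient's quality of life". On timing: "The above observation indicators will be collected on the day before and after treatment", and then "All patients will be followed up for 3 months, and data will be collected according to the same criteria in the first and third months". The Abstract places the 3-month follow-up after 4 weeks of treatment, so there are three separate times after baseline.
- **Section 2.9, Statistical analysis.** A chi-square test is used for counts and a t test or non-parametric test for measurements. One threshold covers them all: "When *P* < .05, the difference is statistically significant". The threshold has no stated side.
- **Section 2.3, Sample size.** "The calculation of sample size is based on mean and standard deviation of scores of Minnesota Living with Heart Failure Questionnaire", taken after treatment. The design values are "Set α = 0.025, unilateral test, β = 0.20", giving 34 per group and 38 after 10% withdrawal.

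**The concern.** Section 2.3 treats the trial as having one decisive test. Sections 2.7 and 2.9 give it two main outcomes of equal standing, and each is called significant at the full .05. Nothing says that both must succeed, that one comes first, or that the threshold is shared. A reader who follows the text could report a positive trial on whichever main outcome crosses .05, and the 5% error rate would then describe each test but not the trial's main conclusion. The choice between the two outcomes would also remain open after the data are seen.

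**Working it through.** **1. The plan's own figure.** Inputs from section 2.3: means 27.91 and 31.12, SDs 4.31 and 4.85, one-sided α 0.025, power 80%.

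- Difference = 31.12 − 27.91 = 3.21.
- Pooled SD = √[(4.31² + 4.85²)/2] = 4.588; standardised difference = 3.21/4.588 = 0.700.
- Exact power (noncentral t, 2n − 2 degrees of freedom, noncentrality 0.700 × √(n/2)): n = 33 gives 79.9%, n = 34 gives 81.1%.
- Withdrawal: 34/0.90 = 37.8, rounded up to 38.

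Both 34 and 38 reproduce. They are right for one test of one outcome at one time.

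**2. Two main outcomes at end of treatment, each at two-sided .05.** The chance of at least one P < .05 when neither outcome differs is 1 − Pr(|Z₁| < 1.96 and |Z₂| < 1.96). The documents give no correlation between the outcomes, so the values below are assumptions.

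| Assumed correlation of the two test statistics | Any false positive | False claim of benefit only |
|---|---|---|
| 0 | 1 − 0.95² = 9.75% | 1 − 0.975² = 4.9% |
| 0.5 | 9.1% | 4.5% |
| 0.7 | 8.3% | 4.2% |
| Single planned test | 5% | 2.5% |

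A direct simulation of a t test and an uncorrected chi-square test with 34 per group, an assumed 75% improvement rate in both groups and latent correlations from 0 to 0.7 gave 9.7–10.1% for the pair. It sits slightly higher because the chi-square test itself rejected in 5.3–5.6% of runs.

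**3. If months 1 and 3 also carried main claims.** That makes 2 outcomes × 3 times = 6 tests. The first correlation is between outcomes, the second between times; both are assumed.

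| Correlations (outcomes / times) | Any false positive among six |
|---|---|
| 0 / 0 | 1 − 0.95⁶ = 26.5% |
| 0.3 / 0.5 | 23.0% |
| 0.5 / 0.7 | 19.2% |
| 0.5 / 0.9 | 14.9% |

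The direct simulation gave 18–27% for six tests over a similar range of latent correlations.

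**4. Does the threshold itself disagree with the sizing?** For a symmetric test, two-sided .05 puts 0.025 in each tail. Read as two-sided, section 2.9 uses the same error rate as section 2.3.

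**The case against.** - **Rules on multiple testing usually sit in a statistical analysis plan, and a journal article condenses.** This is a fair limit on what can be asked. But the article does more than stay silent: it names two main outcomes side by side and fixes one threshold for every difference. An analysis plan would have to restrict that rule, not merely fill it in.
- **No passage says that one significant main outcome makes the trial positive.** This is correct. If both had to be significant there would be no inflation. The text neither states nor excludes either rule, so the 8–10% must carry its condition.
- **The text points to one time, not three.** This largely stands. Section 2.3 sizes on scores after treatment, section 2.7 defines an ineffective result by NYHA class compared before and after treatment, and months 1 and 3 appear only as follow-up data collection. A reader might infer six confirmatory tests and quote an error above 20% as a property of the plan. The documents do not support that, because no main test is set at months 1 and 3.
- **Section 2.3 already implies that MLHFQ is primary.** It does suggest so, but section 2.7 lists the NYHA rate beside it and first. The two sections should say the same thing.

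**Conclusion.** The point holds in a limited form. Two unranked main outcomes under a flat P < .05 do not match a sample size built on one test. If either outcome alone at end of treatment is taken as a positive result, the chance of at least one false positive is about 8–10% two-sided, or about 4–5% against 2.5% for false claims of benefit. This rests on that either-one rule and on assumed correlations from 0 to 0.7. The 15–26% figure applies only if months 1 and 3 were also used for main claims, with correlations from 0.5/0.9 down to independence.

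Two stronger readings are tempting and do not hold:

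- **That sizing and analysis use different alphas.** Two-sided .05 equals one-sided 0.025. A doubled error would need a one-sided test at .05, which no section states.
- **That the lack of a power figure for the NYHA rate is an error.** Section 2.3 says openly that it rests on MLHFQ and claims no power for the other outcome.

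The sample size arithmetic is sound. This is something that should be fixed, not a flaw that invalidates the design.

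**What to change.** Amend sections 2.3, 2.7 and 2.9 so that they agree:

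1. Name MLHFQ at the end of the 4-week treatment, the basis of the sample size, as the primary endpoint, tested at two-sided P < .05 (equal to the planned one-sided 0.025).
2. Test the NYHA improvement rate at the same time second, and only if MLHFQ is significant.
3. Describe months 1 and 3 and the other outcomes as supportive.
4. State that the 80% power refers to MLHFQ only.

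The fixed order keeps the error for the two main outcomes at 5% without splitting alpha, so 34 evaluable and 38 enrolled per group stand. The work is wording only. The real cost is that the NYHA rate, the first-listed main outcome, can no longer carry a positive claim alone.

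If the sponsor wants either outcome to be able to succeed, a Bonferroni split (two-sided 0.025 each) also controls the error. MLHFQ power at 34 per group then falls from 81.1% to 72.2%, and restoring 80% takes 41 evaluable per group, or 41/0.90 = 45.6, rounded up to 46 enrolled. Requiring both outcomes to be significant also avoids inflation, but the chance of meeting both depends on NYHA rates that the article does not give. Whichever rule is chosen, it should be fixed before outcome data are seen.

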## Discussion

3

CHD chronic heart failure is characterized by prolonged disease and poor prognosis, which has a serious impact on the quality of life of patients and even endangers their lives. High-quality nursing is the basis to ensure the therapeutic effect.^[22,23]^

Cluster nursing standardizes various nursing processes based on evidence-based evidence, which can reduce the causes of heart failure, reduce the cardiac load of patients, improve the condition of patients, restore the quality of life of patients, and improve the prognosis of patients.^[24,25]^ However, due to few clinical studies on related topics, cluster nursing has not been widely used in clinical nursing of CHD chronic heart failure. Therefore, this study will explore the impact of cluster nursing on the cardiac function and quality of life of CHD patients with chronic heart failure. At the same time, this study has the following limitations: as this is a single-center randomized controlled study, the included population is regionalized, and the results may be biased to some extent; due to the factors of the intervention program, this study could not achieve strict double blindness, which may have some influence on the results.
